# Postoperative analgesia of scalp nerve block with ropivacaine in pediatric craniotomy patients: a protocol for a prospective, randomized, placebo-controlled, double-blinded trial

**DOI:** 10.1186/s13063-020-04524-7

**Published:** 2020-06-26

**Keywords:** Scalp nerve block, Ropivacaine, Children, Craniotomy, Postoperative analgesia, RCT, Protocol

## Abstract

**Background:**

Moderate-to-severe postoperative pain following craniotomy has a high incidence in pediatric patients. Such pain may cause agitation, intracranial hypertension, epileptic seizures, and postoperative hematoma, which affect morbidity and mortality. Although scalp nerve block (SNB) achieves satisfactory pain relief except for suboccipital mid-craniotomy in adults and ropivacaine is widely used as a long-acting peripheral nerve block agent in children, there are few studies of SNB with ropivacaine in pediatric patients undergoing craniotomy. In addition, the neurosurgery operation time is relatively long, but the duration of action of SNB is limited. It is generally believed that postoperative SNB is better than preoperative SNB for postoperative analgesia. However, considering the concept of preemptive analgesia, we believe that preoperative SNB may achieve a longer postoperative analgesia effect than we expected.

**Methods:**

This trial is a single-institution, prospective, randomized, controlled, double-blind study. A total of 180 children aged between 1 and 12 years who are undergoing elective craniotomy will be randomly allocated in a 1:1:1 ratio to three groups: group B (preoperative ropivacaine block group), group A (postoperative ropivacaine block group), and group N (nonblocking control group). This randomization will be stratified by age in two strata (1–6 years and 7–12 years). The primary outcome is the total consumption of sufentanil within 24 h after surgery. The secondary outcomes include assessment of pain scores, total consumption of sufentanil and emergency-remedy medicine consumption at observation points, the occurrence of postoperative complications, and the length of hospitalization after surgery.

**Discussion:**

This study is designed to explore the effect and feasibility of SNB with ropivacaine for postoperative analgesia in pediatric patients undergoing craniotomy. Further aims are to compare the effects of preoperative and postoperative SNB on postoperative analgesia in order to identify whether there is a preemptive analgesic effect and determine the better time to implement SNB in pediatric patients during craniotomy.

**Trial registration:**

Chinese Clinical Trial Registry ChiCTR1800017386. Registered on 27 July 2018.

## Background

Pain is defined as “an unpleasant sensory and emotional experience associated with actual or potential tissue damage or described in terms of such damage” according to the International Association for the Study of Pain (IASP) [1]. Fetal pain receptors develop at approximately the 26–30th weeks of gestation [2]. Pain can be perceived by individuals ranging from neonates to adolescents, and surgical trauma is an important cause of postoperative pain in children.

For a long time, craniotomy procedures have been considered to be associated with less pain than other surgical procedures; accordingly, fewer analgesic methods are implemented for craniotomies than for other surgical procedures [3]. Therefore, postoperative analgesia of neurosurgery patients has not received sufficient attention. Recently, studies showed that up to 80% of patients experience moderate-to-severe pain after craniotomy [4–10]. There are even fewer investigations on postoperative analgesia in pediatric neurosurgery patients. A study observed that 42% of 52 children undergoing craniotomy continued to experience moderate-to-severe pain within 72 h after surgery and without the use of analgesics [11].

The improper management of pain following neurosurgery may further result in severe consequences such as agitation, intracranial hypertension, epileptic seizures, and postoperative hematoma, which affect morbidity and mortality [12–15] and further lead to a more negative outcome for pediatric craniotomy patients. Moreover, according to long-term follow-up studies, postoperative pediatric pain has a substantial impact on children and may even cause long-term behavioral changes [16]. Currently, opioids are mainly used for the treatment of moderate and severe postoperative pain, but they have clear adverse effects; hence, researchers are exploring alternatives in which nerve block may be a solution for postoperative analgesia following craniotomy [17]. Scalp nerve block (SNB) achieves satisfactory results during either intraoperative awakening or postoperative analgesia, except for suboccipital mid-craniotomy in adults [14, 15, 18–21].

Ropivacaine, for long-action [22] and safety purposes, has become one of the most popular choices in children [23]. However, there are few studies of SNB with ropivacaine in pediatric patients undergoing craniotomy. In addition, the neurosurgical duration is relatively long, and the effective action time of SNB is limited. Postoperative pain is a time-dependent process that is considered to be the most severe within the first 24 h, gradually alleviates, and then disappears substantially at 72 h following surgery. The advantages of SNB following preoperative anesthesia include more stable hemodynamics, better postoperative analgesic effects, and less anesthetic consumption during surgery [24]. However, the duration of the action of SNB is limited. Craniotomy is known to be intricate, and subsequently, more time (typically > 4 h) will be occupied. Postoperative SNB is “timely and fresh” for postoperative analgesic withdrawal, and in theory, its analgesic effect is at least 4 h longer than the preoperative block effect. However, according to the mechanism of “pre-emptive analgesia,” if an analgesic agent is administered before the “tissue damage” occurs, the maximum results will be achieved with a small dose.

Because pain is a subjective indicator and some children, particularly infants, cannot properly express their pain, it is more difficult to evaluate pediatric pain than adult pain [25–27]. There is currently no ideal assessment scale for all pain types in children of all ages. To date, the Face, Legs, Activity, Crying, Consolability (FLACC) scale, Wong–Baker Faces Pain-rating Scale (FACES), and numerical rating scale (NRS) scores have effective assessment instructions for children. The former two scales, which are easily obtained by observers, can assess the pain intensity of children from 1 to 12 years of age. The NRS, which is rated according to the child’s report, can only be used for those aged 7–12 years.

### The Face, Legs, Activity, Crying, Consolability (FLACC) score [28]

The FLACC scale method is commonly used for pain assessment following pediatric surgery. In the FLACC scale, pain scores are obtained by medical staff based on the observed pediatric condition and contents of the quantification table. Each item is scored from 0 to 2 points. The sum of the content scores is the total score (from 0 to 10 points). A higher score indicates more severe pain. With the FLACC scale, physicians observe children for 1–15 min, and this tool is commonly used for the evaluation of postoperative pain in children aged 1–18 years and is the first evaluation method for hospitalized children.

### The Wong–Baker Faces Pain-rating Scale (FACES) facial pain assessment method [29]

This scale is primarily applicable to children between 1 and 18 years of age and for infants or children with communication difficulties. The score ranges from 0 to 10 points. However, it should be noted that children may lose their “smiley face” because of fear, hunger, or other stressors. Therefore, the possible influences of these factors should be excluded from the pain assessment when using this scale.

### The numerical rating scale (NRS)

This scale ranges from 0 to 10 points. A score of 0 indicates no pain, scores of 1–3 indicate slight pain tolerable and does not affect rest, scores of 4–6 indicates that the pain affects sleep but is tolerable, and scores of 7–10 indicate that the pain is intolerable and affects appetite and sleep.

## Methods

### Trial design and study setting

This trial is a single-institution, prospective, randomized, controlled, double-blind study that is designed to explore the effect and feasibility of SNB with ropivacaine for postoperative analgesia in pediatric patients undergoing craniotomy. We further compared the effect of preoperative and postoperative SNB on postoperative analgesia in pediatric craniotomy. From July 2018 to October 2020, pediatric patients aged 1–12 years presenting for elective craniotomies will be recruited from Beijing Tiantan Hospital, Capital Medical University.

The patient flow diagram of the study is presented in Fig. 1, and the study schedule is shown in Table 1.

**Fig. 1 Fig1:**
[figure not shown]
Consolidated standards of reporting trials (CONSORT) flow diagram. Group B: preoperative ropivacaine block group; group A: postoperative nerve block group; group N: nonblocking control group

**Table 1 Tab1:** The schedule of enrollment, interventions, and assessments

		Study period									
		Enrollment	Allocation	Postallocation							
Timepoint		Day − 1	Day 0	After induction, before surgery	After surgery, before extubation	1 h	2 h	4 h	24 h	48 h	Discharge time
Enrollment											
Eligibility screen		X									
Informed consent		X									
Randomization			X								
Allocation			X								
Interventions											
[Group B]	Blocking			X							
	Dressing			X	X						
[Group A]	Blocking				X						
	Dressing			X	X						
[Group N]	Blocking										
	Dressing			X	X						
Assessment											
[Analgesics and remedies]						X	X	X	※	X	
[Pain scores]			X			X	X	X	X	X	
[Complications]						X	X	X	X	X	
[Serious adverse events]						X	X	X	X	X	
[Length of hospitalization]											X

※ primary outcome

### Eligibility

Trial investigators will identify consecutive eligible patients based on the inclusion and exclusion criteria the day before the operation. When patients meet the eligibility criteria, an investigator will explain the study protocol and relevant information to the authorized surrogates and participants. Informed written consent will be obtained from the authorized surrogates and participants (over 7 years) themselves, and then they will be instructed how to use the electronic analgesia pump.

Inclusion criteria:
Age of 1–12 yearsAmerican Society of Anesthesiologists (ASA) physical status of I–IIICraniotomy for tumor resection includes frontal, temporal, parietal, and bifrontal regions.

Exclusion criteria:
Children with severe diseases or cardiac insufficiencyPresence of airway abnormalities and reactive airway diseasesChildren who cannot be weaned from endotracheal intubation following surgeryChildren with abnormal liver and kidney function test results (when alanine aminotransferase, aspartate aminotransferase, blood urea nitrogen, and creatinine levels are higher than or equal to 1.5 times the reference value)Children who have participated in other clinical trialsChildren whose authorized surrogates are unable or unwilling to provide informed consent or poor complianceChildren who have mental illness or use antipsychotic drugs for treatmentPosterior fossa craniotomy for tumor resection

### Allocation and randomization

After meeting the eligibility criteria and signing the informed consent to participate in the study, 180 patients will be randomly allocated in a 1:1:1 ratio to three groups: group B (preoperative ropivacaine block group), group A (postoperative ropivacaine block group), and group N (nonblocking control group), stratified by age into two strata (aged 1–6 years and aged 7–12 years). The allocation schedule will be made with a computer random number list generated by Stata software version 15.1.

### Intervention

The corresponding SNB schemes of the three groups will be the following:
*Group B*: Preoperative SNB group (ropivacaine hydrochloride injection: Naropina®, AstraZeneca AB, Sweden): SNB will be performed after general anesthesia and endotracheal intubation.*Group A*: Postoperative SNB group: SNB will be performed after the end of the operation, and the effects of analgesics and sedatives will not wane.*Group N*: nonblocking control group: This control group will not undergo SNB.

SNB will be performed exclusively by a well-trained anesthesiologist with two age-appropriate concentrations of ropivacaine: 0.3% in children aged 1–6 years and 0.5% in children aged 7–12 years.

The site of SNB will be selected according to the craniotomy region. Dosage: supraorbital nerve (1–2 ml), auriculotemporal nerve (1–2 ml), zygomatic temporal nerve (1–2 ml), greater occipital nerve (2–3 ml), and lesser occipital nerve (2–3 ml). An experienced anesthesiologist will determine the injection points according to the surgical incision site. The total volume will not exceed 5 ml.

The independent anesthesiologist performing the SNB will not be an investigator in charge of the operation and will not visit patients before or after the operation. The anesthesiologist will enter the operating room twice, the first time is after endotracheal intubation prior to surgery, and the second time is after suturing the scalp. He/she will confidentially perform or not perform SNB according to the allocation plan and cover the dressing at the corresponding portion to conceal the allocation. Due to ethical care standards for children, normal saline will not be injected, and only a dressing will be covered in group N.

### Anesthesia and analgesia

On arrival to the operating room, standard monitoring will be established (noninvasive blood pressure (BP), heart rate (HR), pulse oximetry saturation (SpO_2_), invasive arterial pressure, end-tidal carbon dioxide partial pressure (P_ET_CO_2_), anesthesia gas monitoring). Midazolam (0.025–0.075 mg kg^−1^) and methylprednisolone (0.1–0.2 mg kg^−1^) will be received intravenously before anesthesia induction. A dose of 0.5 mg kg^−1^ midazolam will be administered orally to children in whom intravenous access cannot be established due to crying and agitation. Peripheral vascular access will be obtained after sufficient sedation, and anesthesia will be induced with 0.5 μg kg^−1^ sufentanil, 2–3 mg kg^−1^ propofol, and 0.1–0.2 mg kg^−1^ cis-atracurium or 0.4–0.6 mg kg^−1^ rocuronium. After intubation, mechanical ventilation will be in a volume-controlled mode with a tidal volume set at 8–10 ml kg^−1^, and the respiratory rate will be set at 14–20 breaths per minute. Total intravenous infusion anesthesia will be maintained with remifentanil and propofol (8 mg kg^−1^ h^−1^). The initial dose of remifentanil will be 0.1–0.2 μg kg^−1^ min^−1^, adjusted for analgesic needs during operation. The infusion of propofol and remifentanil will be stopped after surgery. Tramadol 1 mg kg^−1^ will be administered half an hour before the end of surgery. The mean arterial pressure (MAP) and HR will be maintained within 30% of the baseline values, and if exceeding this range, corresponding treatment will be taken. No other additional analgesics will be administered during surgery. The total dosage of analgesics and anesthetics will be estimated after surgery. Local infiltration of the head incision will not be performed before surgery. During the operation, the child’s temperature will be monitored and maintained at 35–38 °C. After extubation, patients will be transferred to the postoperative care unit (PACU) or ICU.

At the time of remifentanil halt, an electronic analgesia pump (Apona® electronic infusion pump ZZB-I-150, APON Medical Technology Co., Ltd., Jiangsu, China) will be routinely applied. The electronic analgesia pump includes a bag loaded with 2 μg kg^−1^ sufentanil and 0.3 mg kg^−1^ ondansetron diluted in 100 ml of normal saline. There will be no background infusion doses. Press the electronic analgesia pump when the FLACC pain score is > 4. If the patient is still in the operating room, the anesthesiologist can determine whether to press the button. In the PACU, ICU, or ward, children aged 1–6 will be placed in a nurse-controlled intravenous analgesia mode. Children aged 7–12 will have their analgesia administered by a nurse until they are able to operate the button of the electronic analgesia pump. The electronic analgesia pump will provide a bolus dose of only a 2-ml infusion each time and a lock-out period of 30 min. If the FLACC pain score is > 5 and the FACES facial pain score is > 6, the remedial procedure will be initiated.

Administration of analgesics and remedies: Children who still show insufficient analgesia or discomfort after the operation and require analgesics will be administered acetaminophen at 15 mg kg^−1^ orally. Information on whether additional analgesics will be needed within 3 days after surgery as well as on the drug dosage and frequency and the usage of the postoperative electronic analgesia pump (including total consumption of analgesics and the number of effective compressions and invalid compressions) will be recorded.

### Outcomes measurement

Primary outcome: Total consumption of sufentanil within 24 h after surgery.

Secondary outcomes:
Assessment of postoperative pain scores at 1, 2, 4, 24, and 48 h after surgery: children aged 1–6 years: due to the special characteristics of children after neurosurgery and of preschoolers who cannot properly express their pain with language, two different scoring methods will be used—the FLACC scale and the FACES facial pain score. Children aged 7–12 years can use NRS for self-assessment in addition to the above two methods.Total consumption of sufentanil within 1, 2, 4, and 48 h after surgery and emergency-remedy medicine consumption at 1, 2, 4, 24, and 48 h after surgery.Postoperative safety indicators: complications including agitation, postoperative nausea and vomiting (PONV), bleeding, infection, hypoxemia, respiratory depression, neurological impairment at 1, 2, 4, 24, and 48 h after surgery, and serious adverse events including disability and death.Length of hospitalization after the surgery.

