### Criteria for discontinuing or modifying the allocated interventions

There will be no special criteria for modifying allocated interventions, but there are conditions under which to terminate the study: (1) unexpected postoperative continuation of intubation; (2) serious adverse events during the operation, such as acute massive hemorrhage, malignant fever, and shock; (3) unplanned reoperation within 24 h after surgery; (4) serious, adverse surgically related events/reactions occurring within 24 h after the operation, such as postcraniotomy hematoma, unconsciousness, coma, and cardiac arrest; and (5) serious adverse events/reactions related to the medicines in electronic analgesia pumps within 24 h after surgery.

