### Blinding

After the patient’s enrollment, the independent anesthesiologist who performs the SNB will obtain the allocation randomized schedule from computer software operation. The allocation information of participants who are recruited and randomized will be placed in a sealed envelope and stored individually. Therefore, the anesthesiologist who performs the SNB will be the only person who knows the allocation schedule. This procedure ensures that both investigators and participants will not know the intervention.

Patients, anesthesiologists in charge of operation, and investigators who are responsible for enrolling and observing the primary and secondary outcomes will not know whether the children will receive blocking. The blinding will be discontinued after all data collection is completed. Furthermore, serious life-threatening adverse events leading to prolonged hospital stay or death will be reported to the principal investigator (PI), and the blinding will be broken following consultation with the PI if necessary.

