## Discussion

All pediatric patients who undergo craniotomy require analgesic medications for postoperative analgesia. SNB is a simple strategy that can relieve postoperative pain. In this trial, we hypothesize that ropivacaine, which is the SNB administered in pediatric patients undergoing neurosurgery, will decrease the requirement for sufentanil and other pain medications as well as reduce postoperative pain scores. The second aim is to determine whether preoperative block or postoperative block is more suitable for postoperative pain control. This study will be a prospective, randomized, controlled, double-blind study. Participants are randomized into three groups: preoperative SNB group, postoperative SNB group, and nonblocking control group, who will be followed for 48 h postoperatively and then the day of discharge. We have set the same standardized anesthesia protocol to avoid sources of bias and will use the FACES facial pain assessment method based on the FLACC scale to improve the accuracy of pain measurement. The study will be carried out at Beijing Tiantan Hospital, Capital Medical University (which has the highest rank for neurosurgery in China). This investigation is a single-center study, which may bias our results. However, the results of this study may promote the development of postoperative analgesia and popularize the optimal pain management of children.

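### Complications and, in Table 1, serious adverse events stop at 48 h although children are followed to discharge, so later in-hospital events have no scheduled by-group collection

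*Protocol article*

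**What the plan says.** Outcomes measurement names the complications to be counted, among them "bleeding, infection, hypoxemia, respiratory depression", and closes the list with "neurological impairment at 1, 2, 4, 24, and 48 h after surgery, and serious adverse events including disability and death". The five times attach to the complications; the clause on serious adverse events carries no time of its own.

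Table 1 has a row for complications and a row for "Serious adverse events". Both are marked at 1, 2, 4, 24 and 48 h. The table also has a discharge column, but only the row "Length of hospitalization" is marked there. Data collection and management ends the blinded investigator's ward visits at 48 h.

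Three other places use different periods:

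- The Discussion describes participants "who will be followed for 48 h postoperatively and then the day of discharge".
- The Blinding section says that "serious life-threatening adverse events leading to prolonged hospital stay or death will be reported to the principal investigator (PI"), with no time limit.
- Anesthesia and analgesia records "Information on whether additional analgesics will be needed within 3 days after surgery", together with pump use, whereas the analgesic row of Table 1 ends at 48 h.

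**The concern.** The trial adds needle injections to the scalp, at points chosen by incision site, in two of its three groups. It names infection and neurological impairment among its own safety indicators. If the forms follow Table 1, a child who develops an infection or a new deficit after the 48 h visit but before going home contributes a longer stay and no recorded event.

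What is at stake is the complication table. Readers will use it to judge whether the block is acceptable in children. Low counts in all three groups could be taken as evidence about the whole admission when they describe only the first two days. The serious adverse event row has a further problem: the article gives no single answer to how long these events are collected.

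**Working it through.** **Step 1: set the periods side by side.**

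| Item | Place in the article | Period stated |
|---|---|---|
| Complications | Outcomes measurement; Table 1 | 1, 2, 4, 24, 48 h |
| Serious adverse events | Table 1 | 1, 2, 4, 24, 48 h |
| Serious adverse events | Outcomes measurement | none stated |
| Life-threatening serious events reported to the PI | Blinding | none stated |
| Ward visits | Data collection and management | to 48 h |
| Length of stay | Table 1; Outcomes measurement | at discharge |
| Follow-up of the child | Discussion | 48 h, then day of discharge |
| Additional analgesics and pump use | Anesthesia and analgesia | 3 days |
| Analgesics and remedies | Table 1 | to 48 h |

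For complications the two sources agree, and both stop at 48 h. For serious adverse events Table 1 stops at 48 h and the other two places do not. The route in the Blinding section covers life-threatening events only and exists for reporting and possible unblinding. It would not produce a by-group count of infections or neurological deficits.

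**Step 2: denominators.** Sample size gives 54 per group and 10% loss. 54 / (1 − 0.10) = 60 per group, and 3 × 60 = 180. This reproduces the plan's figure. Two of the three groups receive the block: 2 × 60 = 120.

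**Step 3: illustration.** The article gives neither event rates nor timing, so no corrected figure can be derived. Assume an in-hospital infection risk p of 2% or 5%, and a share f of infections arising after 48 h of 25% to 90%. Both ranges are assumptions.

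- Expected outside the schedule: 180 × p × f
- Expected inside the schedule: 180 × p × (1 − f)
- Chance of seeing at least one among the block patients: 1 − [1 − p(1 − f)]^120

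| p | f | Outside, of 180 | Inside, of 180 | Inside, per group | At least one seen in 120 |
|---|---|---|---|---|---|
| 2% | 0 | 0 | 3.6 | 1.2 | 91% |
| 2% | 25% | 0.9 | 2.7 | 0.9 | 84% |
| 2% | 50% | 1.8 | 1.8 | 0.6 | 70% |
| 2% | 90% | 3.24 | 0.36 | 0.12 | 21% |
| 5% | 0 | 0 | 9 | 3 | 99.8% |
| 5% | 25% | 2.25 | 6.75 | 2.25 | 99% |
| 5% | 50% | 4.5 | 4.5 | 1.5 | 95% |
| 5% | 90% | 8.1 | 0.9 | 0.3 | 45% |

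The rows with f = 0 show what collection to discharge would give.

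**Step 4: what a zero count would mean.** With no events in n children, the one-sided 95% upper bound on the risk is 1 − 0.05^(1/n): 4.9% for n = 60 and 2.5% for n = 120. Under the present schedule these bounds apply to the first 48 h and say nothing about the rest of the stay.

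**The case against.** The strongest reply is that this is a condensed article about a trial whose primary outcome is sufentanil use over 24 h. The detailed reporting period for serious adverse events may well be in the full protocol. That is a fair defence against a charge of omission. It does not answer Table 1, which sets out a schedule, includes a discharge column, and leaves it blank for these rows. The Discussion's mention of the day of discharge could also mean only that the date is noted. Even so, the child's record is consulted at that point, so later events could be taken from it.

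Four stronger readings are tempting, and the documents do not support them.

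- *Prolonged stay is missed.* It is not. Length of hospitalization is a secondary outcome recorded at discharge. What is lost is the event behind a longer stay.
- *No serious event after 48 h would be recorded.* This is too absolute. Outcomes measurement sets no limit, and a late life-threatening event or death has the open-ended route to the principal investigator.
- *Block safety is overstated.* The schedule is identical in three randomized groups, including the nonblocking control. It lowers counts and precision everywhere, and no direction of bias is shown. Nor does the article plan any statement of no difference in complications.
- *Pump-related reactions are followed for only 24 h.* The wording "serious adverse events/reactions related to the medicines in electronic analgesia pumps within 24 h after surgery" is one of the conditions for ending a child's participation, not a collection window. Complications and serious adverse events are still scheduled at 48 h, the last time for which sufentanil consumption is an outcome.

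The 3-day recording of analgesics is a minor mismatch: it collects more than the outcome list uses and loses nothing.

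**Conclusion.** The point holds in a limited form. Infection, bleeding, neurological impairment and non-life-threatening serious events between 48 h and discharge have no scheduled by-group collection, and the serious adverse event period differs between Table 1, Outcomes measurement and Blinding. Absolute in-hospital rates would be understated in every arm, and the group comparison would be uninformative about late events.

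The size cannot be fixed from the article. Under the assumed 2% to 5% risk and 25% to 90% late share, 0.9 to 8.1 infections among 180 children would go unscheduled. The chance of seeing even one among 120 block patients would fall from 91% to between 84% and 21% at 2% risk, and from 99.8% to between 99% and 45% at 5%. If few such events arise after 48 h, little is lost. The primary outcome and the sample size are unaffected. This is a cheap improvement to the trial's own safety outcome, worth making but not critical.

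**What to change.** 1. In Table 1 and Outcomes measurement, mark serious adverse events, infection, bleeding and neurological impairment at the existing discharge time point, recorded as any occurrence since 48 h, with its date.
2. Report these by group to discharge, alongside the 48 h tabulation.
3. State one collection period for serious adverse events and use it in Table 1, Outcomes measurement and Blinding.
4. Reconcile the 3-day recording of additional analgesics and pump use with the 48 h schedule.
5. If the discharge collection is not added, limit safety conclusions to the first 48 h and say so in the report.

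The cost is one further line on the discharge form, filled from the hospital record at a time point already scheduled. Data entry rises slightly. Late events will include surgical ones unrelated to the block; randomization balances these on average, but they add noise to the comparison.
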